### Randomization, blinding and quality assurance

Randomization was achieved using a computer-based random number sequence. Once written consent was obtained, participants were enrolled in the study. Baseline assessments were then completed and BMI status was checked and the women were categorised as healthy weight or overweight. At the end of the first assessment the enrolled women were given a participant identification number by a researcher ([name]). The numbers used were from a random allocation sequence generated by a statistician using a computer-based random number-producing algorithm to ensure an equal chance of allocation to each intervention group (the Plan procedure (Proc Plan) in the SAS statistical software package) in block lengths of six. The sequence was divided into two separate lists — one for each BMI category. [name] checked the BMI category of each participant at the conclusion of the first assessment, then allocated the participant to the next vacant number sequence on either the healthy weight list or the overweight list as appropriate. This ensured approximately equal numbers of healthy weight and overweight women were assigned to each intervention group. [name] remained blinded to group assignment. A separate version of each list, with intervention group appearing next to each identification number was only given to one researcher ([name]) who was unable to remain blinded after baseline measures since she delivered the face-to-face Dietitian consultations. She phoned the women within a day of their baseline measures to inform them of their group assignment.

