### Goals of the intervention

Both the MI and SDI women were given intervention goals according to their baseline BMI as shown in Additional file 1. Women found to be in the healthy weight range (18.5 – 24.9 kg/m^2^) at baseline were advised to maintain that weight within 1 kg for the duration of the study. Written advice was provided in booklet format so the women could meet their Recommended Dietary Intakes (RDI) for micronutrients and macronutrients [29] and an intake of 8300 kJ/day, which is the estimated requirement for women 51–70 years with a mean height of 1.6 m and an activity factor of 1.6 [29]. The booklet also outlined how to meet physical activity recommendations of at least 150 mins/week of moderate intensity physical activity [30], 10000 steps per day [31] and restriction of sitting time to 3 hr/day or less [23,32].

Women with a baseline BMI in the overweight range (25–29.9 kg/m^2^) were advised to lose up to 7% of baseline weight (an amount shown in previous interventions to have significant clinical outcomes for the overweight) [33]. Written advice was provided in booklet format to meet the same RDIs as the healthy weight women, within a maximum energy intake of 6300 kJ/day, which is 2000 kJ less than the estimated requirement for weight maintenance of 8300 kJ [29] in order to achieve a weight loss of approximately 0.5 kg per week. Physical activity advice was increased to 250 mins/week of moderate intensity to help achieve weight loss [34], with the same daily step count and sitting time as the healthy weight group.

A protocol responding to changes in BMI category was developed. It stated that, if in achieving their weight loss goal the overweight women achieved a BMI in the healthy weight range, they were advised to maintain that new weight within 1 kg for the remainder of the study and would be given the written booklet containing advice prepared for healthy weight women. Conversely, any healthy weight women found to have gained sufficient weight to be reclassified as overweight would be given the written advice and behavioural goals for the overweight women, and advised to lose weight to re-attain the healthy weight range. The process for change in goals is shown in the Figure in Additional file 1.

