### Sample size

The sample size calculation was based on the main outcome measure of body weight. Observational studies of women in this age group in the Australian population have demonstrated a mean (SD) weight gain of 1.04 (4.7) kg over a two-year period [22]. Given both intervention groups were comprised of equal numbers of healthy weight and overweight women and presuming the overweight women would meet the intervention goal of losing 5 kg^a^ in the first 12 months and the healthy weight women would show zero weight change, the net weight change should be a 2.5 kg weight loss in the MI group by the end of phase 1. Based on the Australian data of net weight gain in the general population of mid-age women managing their weight by self-directed means [21], we would expect a mean (SD) net weight gain of 0.5 (4.7) kg per year in our SDI (control) group. This would give an expected difference between the two groups of 3.0 kg after 12 months (end phase 1) and 3.5 kg after 24 months (end phase 2). Assuming equal sample sizes, to detect a difference in weight between groups of 3.5 kg with 80% power and a significance level of 0.05, a sample size of 22 women was required for each group. Allowing for an attrition rate of 20% by the end of 24 months, a total sample size of 55 women is required.

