### Outcome measures

Outcome measures were assessed for all participants at baseline, between May-September 2010, and reassessed at 3, 12, 18 and 24 months (end of monitoring phase 2) as shown in Additional file 3. The primary endpoints are at 12 months to determine the effects of the intervention and at 24 months to assess whether the intervention effects were maintained. Weight was the primary outcome measure.

#### **
*Measurement procedure*
**

Assessments were conducted in the early morning, in the anthropometry laboratory at the University of Newcastle (Australia). Procedures and protocols for the measurements were standardised, documented, and research assistants were trained in their application prior to collection. Participants fasted overnight, and upon entry to the laboratory removed their shoes and excess clothing. The assessment process lasted approximately 60 minutes for each participant, and they were provided with breakfast prior to leaving the laboratory.

#### **
*Anthropometry*
**

Height was measured using a stadiometer (Surgical and Medical Products) correct to 0.1 cm using the stretch stature method. Weight and body composition (percentage fat, skeletal muscle mass) were measured at all time points using BIA Omron HBR-500 Body Composition Monitor with Scales correct to 0.1 kg. BMI was calculated using the standard equation (weight [kg]/height[m]^2^). Waist circumference was collected as a valid marker of central adiposity [44] using a non-extensible steel tape to measure at the level of the mid-point between the lower costal border and the iliac crest (KDS F10-02, KDS Corporation, Osaka, Japan). Two measures were collected and averaged. Visceral adipose tissue area was estimated using the InBody720 Body Composition Analyzer (Biospace) at 12, 18 and 24 months.

#### **
*Biomarkers of metabolic syndrome*
**

Thirty millilitres of blood was collected from each participant by a trained phlebotomist and analysed by a laboratory accredited with the National Association of Testing Authorities Australia. Fasting measures of total cholesterol, low density lipoprotein cholesterol, high density lipoprotein cholesterol, triglycerides and glucose were assessed. Blood samples have been stored in a -80°C freezer for further analyses (sex hormones, insulin, leptin, and antioxidants to validate dietary intake) should funds become available.

#### **
*Blood pressure and resting heart rate*
**

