### Data analysis

Outcome measures collected at baseline will be compared to those at 12 months (after adjusting for baseline weight) to assess intervention effects and compared with measures at 24 months (end phase 2) to assess whether the intervention effects were maintained. Analyses will be conducted using the intention to treat principle, and performed using SPSS version 19 (IBM). All variables will be checked for plausibility. Continuous variables will be assessed for normality. Independent sample t-tests and chi-squared tests will be conducted on continuous and categorical variables (respectively) to check they do not vary by intervention group at baseline, and by completers versus attriters. Analysis of covariance will be used to examine whether the intervention groups differed significantly in weight at each of 12 and 24 months after adjusting for baseline weight. Behaviour changes in diet and physical activity will be assessed as secondary outcome measures using analysis of covariance to determine whether the MI and SDI groups differed significantly in dietary or physical activity behaviours at 12 months. Results will be stratified for baseline BMI category.

Logistic regression analysis will be performed to assess whether categorical variables, such as smoking status significantly influenced weight. The visceral adipose tissue variable will be assessed for between group differences at 12 and 24 months using independent sample t-tests, and analyses stratified by BMI category to determine whether the results differed for the healthy weight and overweight women. Sensitivity analyses will be conducted to determine the effects on the outcomes of different methods of treating loss to follow-up (last observation carried forward versus imputation). The relationship between weight outcomes and compliance with the diet and physical activity behaviours will be assessed using mediation analysis [55].

A per protocol analysis will be conducted on women who adhered to the requirements of their assigned group. Adherent women are defined as those who completed all required eating and physical activity diaries over the 12-month period and attended all assessment sessions, regardless of assigned group, and who attended all five health professional consultations for the MI group. Results of the protocol adherent group will be compared with non-adherers in each group, that is, those who did not meet the adherence recommendations.

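### The primary weight ANCOVA names only baseline weight and does not clearly include BMI category, the randomisation stratum; the result stays valid, but a small, nearly free gain in precision is left unspecified

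*Protocol article*

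**What the plan says.** All references are to the protocol article.

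- **Outcome measures:** "Weight was the primary outcome measure", with endpoints at 12 and 24 months.
- **Data analysis:** the ANCOVA asks whether the arms "differed significantly in weight at each of 12 and 24 months after adjusting for baseline weight". Diet and physical activity at 12 months are also compared by ANCOVA. The paragraph then ends: "Results will be stratified for baseline BMI category".
- **Randomization, blinding and quality assurance:** "The sequence was divided into two separate lists", one for each BMI category, in blocks of six.
- **Goals of the intervention:** "Both the MI and SDI women were given intervention goals according to their baseline BMI as shown in Additional file 1". Healthy-weight women were to hold their weight within 1 kg. Overweight women were to lose up to 7%, with different energy and activity targets.
- **Sample size:** the MI effect is built by "presuming the overweight women would meet the intervention goal of losing 5 kg" while "the healthy weight women would show zero weight change". The SDI arm is given one average gain, with no split by category.

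**The concern.** BMI category is the variable on which allocation was stratified. On the plan's own assumptions it is also related to weight change, at least in the MI arm. An analysis normally carries its stratification factor. If the factor is left out, the variation it explains stays in the residual, although stratified allocation has already balanced it between arms. The reported standard error is then larger than the true sampling error and the test is slightly conservative. In a trial planned on 22 women per arm, even small losses deserve attention. There is also a question of pre-specification: as worded, the reader cannot tell whether the overall comparison, a category-adjusted comparison or the two category-specific comparisons carry the primary claim.

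**Working it through.** **1. The plan's own figure.** The Sample size section seeks "to detect a difference in weight between groups of 3.5 kg with 80% power and a significance level of 0.05", with SD 4.7 kg, and states 22 per group. With n = 2(z_alpha + z_beta)²(SD/difference)²:
- one-sided: 2 × (1.645 + 0.842)² × (4.7/3.5)² = 22.3 (23 with the t correction)
- two-sided: 2 × (1.960 + 0.842)² × (4.7/3.5)² = 28.3, so 29

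44/(1 − 0.20) = 55 reproduces the total. So 22 is reached only with a one-sided test. That is a separate matter; 22 per arm is used here only to fix the scale. All power figures below are two-sided at 0.05.

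**2. Inputs for the covariate question.**
- From the article: 22 per arm; half of each arm in each category; SD 4.7 kg; MI changes of 0 and −5 kg; SDI +0.5 kg at 12 months and +1 kg at 24 months in both categories.
- Assumed, not in the article: 4.7 kg is the SD within category; mean height about 1.63 m with SD 6.5 cm, which gives a correlation of about 0.72 between category and baseline weight. Height SDs of 4 to 8 cm give 0.82 down to 0.67.

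**3. Arithmetic check, 24 months.** The overweight-minus-healthy gap is −5 kg in MI and 0 in SDI. The average gap is therefore −2.5 kg, and each arm departs from it by 2.5 kg. Residual variance:
- baseline weight only: 22.09 + 0.25 × 2.5² × (1 − 0.72²) + 0.25 × 2.5² = 22.09 + 0.75 + 1.56 = 24.40, SD 4.94
- plus category: 22.09 + 1.56 = 23.65, SD 4.86
- plus category and arm-by-category: 22.09, SD 4.70

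Multiplying by √(2/22) = 0.3015 gives SEs of 1.49, 1.47 and 1.42. Once category is in the model, chance imbalance in weight within category adds about 0.6%, so 1.47 becomes about 1.48. The gain from category alone is about 1%.

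With a 5 kg gap in both arms, the weight-only variance is 22.09 + 0.25 × 25 × 0.4816 = 25.10, SE 1.51. With category it is 22.09, SE 1.42, or about 1.43 after the same 0.6%. That is a gain of about 6%.

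**4. Simulation** (mean height 1.638 m, SD 6 cm, correlation 0.75, within-category SD 4.7 kg). Each cell gives mean model SE and rejection rate.

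| Scenario (healthy / overweight change, kg) | Weight only | + category | + category and arm-by-category |
|---|---|---|---|
| Plan, 24 months: MI 0/−5, SDI +1/+1 | 1.489, 64.4% | 1.478, 65.2% | 1.426, 67.9% |
| Plan, 12 months: MI 0/−5, SDI +0.5/+0.5 | 1.496, 49.8% | 1.485, 50.4% | 1.433, 53.4% |
| Gap in both arms: MI +1/−6, SDI +2/0 | 1.537, 60.1% | 1.477, 63.0% | 1.425, 65.7% |
| No arm effect, 5 kg gap in both arms | 1.509, 4.3% | 1.429, 4.9% | 1.430, 4.9% |
| No arm or category effect | 1.415, 5.0% | 1.425, 4.9% | 1.425, 4.9% |

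In the first row the actual sampling SD of the weight-only estimate is 1.443, against 1.438 with category. The estimate itself is hardly less precise; its reported SE is a little too large. Coverage of the weight-only interval was 95.0% to 97.0% across scenarios.

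**5. Sensitivity.** With height SD 6.5 cm, the plan's 24-month effects give SE 1.49, 1.48 and 1.42 and power 62.5%, 63.4% and 66.6% for the three models. With a 5 kg gap in both arms and the 3.5 kg arm effect, category alone takes SE from 1.51–1.52 to 1.43 and power from 61–62% to 66–67%. Across height SDs of 4 to 8 cm and within-category SDs of 4.0 to 4.7 kg, category alone narrows the interval by 0.2% to 1.7% under the plan's effects.

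**6. What stratified results means here.** In the next paragraph of Data analysis, stratified analyses of visceral fat are said to serve the question of whether results differ between healthy-weight and overweight women. That describes separate results, not a term in an overall model.

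**The case against.** The strongest reply has three parts.

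First, the stratification sentence follows directly on the weight and behaviour ANCOVAs, and the text does not rule out a model factor. That stands as far as it goes: the fair description is that the role of BMI category is unclear, not that it is certainly excluded. The visceral-fat wording makes separate results the likelier meaning.

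Second, this is a journal article, and a fuller plan may list covariates. But the article does state the adjustment for the primary test, and the stratum is not in it.

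Third, baseline weight already carries most of what category would add. This stands, and it is why the loss is small. Calling baseline weight a weak stand-in would not fit a correlation near 0.72.

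Three stronger readings are tempting and are not supported:
- **That the primary test is wrong.** The estimate is unbiased, and the test errs on the safe side (4.0% to 4.4% type I error with a 5 kg gap in both arms).
- **That the omission costs 3 to 4 points of power under the plan's effects.** Most of that gain comes from the arm-by-category term, which adjusting for a stratification factor does not require.
- **That the MI-arm SD is really √(4.7² + 2.5²) = 5.3 kg.** This takes 4.7 kg as a within-category SD, whereas the article draws it from population data on mid-age women. It is in any case a sample-size question.

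**Conclusion.** The point holds as a minor matter of specification and efficiency. The stated primary model does not clearly contain the randomisation stratum. Under the plan's own effects, adding category alone is worth about 1% of interval width and about 1 point of power. It reaches about 6% in SE and about 5 points only if a 5 kg category effect appears in both arms. The plan does not assume this, although both arms receive category-specific goals. If category adds nothing beyond weight, the cost is about 0.6% in SE.

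These sizes rest on the assumed height distribution, an even split of categories and a 4.7 kg within-category SD. No size was calculated for the diet and activity outcomes; the case there rests on the targets differing by category. Removing the ambiguity about which comparison is primary is worth at least as much as the precision.

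**What to change.** State the primary model at each of 12 and 24 months as weight = arm + baseline weight + BMI category, where category is the list from which the woman was allocated. Add the same factor to the 12-month diet and activity ANCOVAs. Replace the stratification sentence with one saying that category-specific effects will be reported from a separate model with an arm-by-category term.

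Putting that term, centred, into the primary model is optional. It would add about 3 to 4 points of power under the plan's effects, but whether a trial of this size should carry it there is open to debate.

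The cost is one sentence and one degree of freedom out of about 40 (two with the optional term). BMI category was determined for every woman before allocation, so no new data are needed.

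### Logistic regression is named for a secondary question about what influenced weight, but weight is a continuous outcome in kg and no binary weight outcome is defined for it

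*Protocol article*

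**What the plan says.** The sentence at issue is in the second paragraph of Data analysis: "Logistic regression analysis will be performed to assess whether categorical variables, such as smoking status significantly influenced weight".

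The rest of the article treats weight as a continuous quantity:

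- Outcome measures: "Weight was the primary outcome measure". It is taken with a "BIA Omron HBR-500 Body Composition Monitor with Scales correct to 0.1 kg".
- Study aim: both hypotheses are stated as changes in kg.
- Sample size: "we would expect a mean (SD) net weight gain of 0.5 (4.7) kg per year in our SDI (control) group", and the study is sized "to detect a difference in weight between groups of 3.5 kg with 80% power and a significance level of 0.05".
- Data analysis, in the paragraph just before the disputed sentence: "Analysis of covariance will be used to examine whether the intervention groups differed significantly in weight at each of 12 and 24 months", with adjustment for baseline weight.

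No section names a binary or categorised weight variable as the outcome of the logistic model.

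**The concern.** What decides between linear and logistic regression is the type of the dependent variable, not the type of the predictors. A categorical predictor such as smoking status is an ordinary factor in a linear model. The sentence appears to choose logistic regression because the explanatory variables are categorical.

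An analyst who follows the text has two options, and neither answers the question asked. One is to make smoking the dependent variable and weight the predictor. The other is to cut weight into classes at a threshold that the article does not give. The second option discards information in a small trial and leaves the threshold open to choice after the data have been seen.

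**Working it through.** The article states no figure for this analysis, so the main check sets model type against outcome type. The arithmetic only sizes one of the two readings.

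**1. Roles of the variables.** In the quoted sentence the categorical variable does the influencing and weight is influenced. The dependent variable is therefore weight, in kg to 0.1 kg.

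**2. What logistic regression would require.**

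- Reading (a): smoking status is the dependent variable and weight the predictor. The model fits, but it estimates the odds of smoking per kg, not a difference in weight by smoking status.
- Reading (b): weight is made categorical. Ordinal and multinomial versions also belong here, since they too need cut-points.

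**3. Does the article supply a cut-point?** There are three candidates:

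- Goals of the intervention gives healthy-weight women a 1 kg maintenance band. This is advice to participants, not an analysis endpoint.
- The same section gives overweight women a loss of up to 7%. This is a ceiling with no minimum, so it does not separate success from failure.
- The Dietary restraint paragraph refers once to success in controlling weight. It does not define this, and the context is the eating questionnaire.

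None is linked to the logistic model.

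**4. Cost of reading (b).** For a normal outcome cut so that a proportion p lies on one side, the asymptotic efficiency relative to the uncut outcome is φ(z_p)² / [p(1 − p)], where φ is the standard normal density and z_p the p-quantile. It is largest at the median, where it equals 2/π.

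| Cut | Relative efficiency |
|---|---|
| 50/50 | 0.64 |
| 30/70 | 0.58 |
| 20/80 | 0.49 |
| 10/90 | 0.34 |

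The planned number of completers is 2 × 22 = 44 ("a sample size of 22 women was required for each group"). This agrees with "Allowing for an attrition rate of 20% by the end of 24 months, a total sample size of 55 women is required", since 44 / (1 − 0.20) = 55. The Abstract gives 28 + 26 = 54 randomised. At the best cut:

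- 44 × 0.637 = 28.0, so 44 completers carry the information of about 28.
- 54 × 0.637 = 34.4, so 54 women, all followed up, carry that of about 34.

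**5. Simulation, on assumed inputs.** SD 4.7 kg comes from the article. The covariate effect of 3.5 kg and both prevalences are assumptions, because the article gives neither for smoking. Over 4,000 runs, a t-test on continuous weight was compared with a logistic likelihood-ratio test after a median split:

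| N | Covariate prevalence | Power, linear | Power, logistic | Runs with an empty cell |
|---|---|---|---|---|
| 44 | 50% | 0.67 | 0.43 | 0% |
| 54 | 50% | 0.77 | 0.51 | 0% |
| 44 | 15% | 0.43 | 0.40 | 10.6% |
| 54 | 15% | 0.48 | 0.33 | 8.3% |

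The balanced rows show the expected loss. At 15% prevalence the smaller group has only about 7 or 8 women. The true size of the likelihood-ratio test was not checked at such counts, so those power gaps should not be read closely. The useful result there is that about 8 to 11% of data sets have an empty cell, for which the logistic estimate is not finite.

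**The case against.** **A binary outcome may have been intended.** The article uses weight categories throughout: healthy weight against overweight, reclassification during follow-up, and compliance with weight goals. Logistic regression on goal attainment or BMI category would be legitimate. The fault would then be an unnamed dependent variable, which a condensed article may leave to a fuller plan. This softens the point but does not remove it. The sentence says weight, not goal attainment, and nothing ties any of these categories to the model. The article does not just omit a detail; it names a model that does not fit the outcome in the same sentence.

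**Reach.** A reader might infer that the efficacy result is compromised. The documents do not support this. The treatment comparison is an ANCOVA of weight at 12 and 24 months. No hypothesis, primary endpoint or sample-size input depends on the disputed sentence.

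**Magnitude.** A reader might also infer that the trial will lose about a third of its information. That does not follow either. The 64% figure applies only under reading (b), only at a median split and only to this covariate question. The article proposes no such split. The figure of 34 women further assumes that all 54 are followed up, whereas the article plans for 20% attrition.

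**Targets.** The article does not promise an adjusted kg estimate from this step or a model combined with the ANCOVA. Missing those is not in itself an error. The error is the mismatch between model and question.

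**Conclusion.** The point holds for one secondary analysis. The named method does not fit the named outcome, and no section resolves this. Under one reading the analysis answers the reverse question. Under the other it needs an unstated cut of weight and keeps at most about 64% of the information: about 28 of 44 completers, or 34 of 54 randomised women. More unequal cuts keep less, down to 34% at 10/90. These sizes assume a normal outcome and large-sample efficiency, and they are conditional on dichotomising. The primary ANCOVA and its conclusions are unaffected.

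**What to change.** Amend the one sentence. For this secondary question, use linear regression or ANCOVA of weight at 12 and at 24 months. Enter smoking status, and any other categorical variable listed in advance, as a factor alongside baseline weight and intervention group. Report differences in kg with 95% confidence intervals. Run this separately from the primary ANCOVA so that the primary model does not change.

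Keep logistic regression only if a binary weight outcome is wanted, and then name that outcome with its cut-point and time point.

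The linear model needs no new weight measurement. The statistical cost is small but not nil. With 44 completers, an intercept, baseline weight, group and one two-level factor leave 44 − 4 = 40 residual degrees of freedom, and each further level takes one more. Some factor levels may be sparse: at an assumed 15% prevalence, 0.15 × 44 = 6.6, or about 7 women. The list of variables should therefore be short.

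Possible wording: *In secondary analyses, separate from the primary ANCOVA, the association of smoking status with weight at 12 and 24 months will be estimated by linear regression with baseline weight and intervention group in the model.*

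### The overall visceral fat comparison is an unadjusted t-test that leaves out the BMI randomisation stratum and recorded baseline adiposity; the general adjustment phrase is also ambiguous for non-weight outcomes

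*Protocol article*

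**What the plan says.** Under Outcome measures (Anthropometry), the article lists the visceral fat schedule: "Visceral adipose tissue area was estimated using the InBody720 Body Composition Analyzer (Biospace) at 12, 18 and 24 months". Baseline and 3 months are not listed. The other body composition measures have a fuller schedule: "Weight and body composition (percentage fat, skeletal muscle mass) were measured at all time points". Waist circumference was also taken at baseline, as the section on randomization, blinding and quality assurance confirms. That section also says that allocation used a separate list for each BMI category, in blocks of six.

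Under Data analysis, the test for visceral fat is fixed: "The visceral adipose tissue variable will be assessed for between group differences at 12 and 24 months using independent sample t-tests". The same sentence adds "analyses stratified by BMI category to determine whether the results differed for the healthy weight and overweight women". No covariate is named.

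For outcomes in general, the section opens with "Outcome measures collected at baseline will be compared to those at 12 months (after adjusting for baseline weight) to assess intervention effects". Two models are then specified:

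- Weight: ANCOVA to examine "whether the intervention groups differed significantly in weight at each of 12 and 24 months after adjusting for baseline weight".
- Diet and physical activity: assessed "using analysis of covariance to determine whether the MI and SDI groups differed significantly in dietary or physical activity behaviours at 12 months", with no covariate named.

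The Discussion concedes that the study is underpowered for secondary outcomes.

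**The concern.** With no baseline visceral fat value, the usual own-baseline adjustment is impossible. The next best step is to adjust for baseline variables related to visceral fat. Several were recorded before allocation, and one of them, BMI category, defined the randomisation strata. The named test uses none of them.

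This has two consequences. First, variation between healthy weight and overweight women, and between leaner and fatter women within each category, stays in the standard error. Because allocation was stratified by BMI category, the design already largely balances that factor. A pooled t-test that ignores the factor therefore reports a standard error that is too large. Second, any chance imbalance in adiposity within a BMI category passes uncorrected into the estimated difference. Both matter more in a trial planned for about 22 completers per arm.

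The general sentence raises a smaller issue. Read literally, it makes baseline weight the covariate for every outcome. For steps, diet, blood pressure, lipids or SF-36 scores, the outcome's own baseline is the natural covariate.

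**Working it through.** **Inputs from the article.** Planned completers are 22 per group (Sample size), and 44/0.8 = 55 reproduces the stated total. No effect size, SD or correlation is given for visceral fat or any other secondary outcome, so there is no stated figure for this point to reproduce. The 22 is used here only as the planned arm size. The weight calculation behind it gives 29 per arm at two-sided 0.05 and 23 at one-sided 0.05 (3.5 kg, SD 4.7 kg, 80% power), but that is a separate matter.

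**Assumption.** r is the correlation between the baseline covariate and visceral fat at follow-up. The documents do not give it, so a range is shown.

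**Step 1: effect of one covariate.** Residual variance is multiplied by 1 − r² (ignoring the small loss of degrees of freedom). With 22 per arm, two-sided 0.05 and 80% power, the detectable difference in SD units is (1.96 + 0.84) × √(2/22) × √(1 − r²) = 0.845 × √(1 − r²).

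| r | 1 − r² | Detectable difference (SD) | Power for 0.5 SD |
|---|---|---|---|
| 0 (planned t-test) | 1.00 | 0.845 | 38% |
| 0.3 | 0.91 | 0.806 | 41% |
| 0.5 | 0.75 | 0.732 | 48% |
| 0.7 | 0.51 | 0.603 | 64% |

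**Step 2: BMI stratum alone.** With two equal strata whose means differ by d within-stratum SD, the stratum explains (d²/4)/(1 + d²/4) of total variance:

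- d = 0.5: 0.0625/1.0625 = 6%
- d = 1.0: 0.25/1.25 = 20%
- d = 1.5: 0.5625/1.5625 = 36%

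The values of d are assumptions.

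**Step 3: chance imbalance.** The standard error of a baseline mean difference is √(2/22) = 0.30 SD. At r = 0.7, an imbalance of one standard error moves the unadjusted result by 0.7 × 0.30 = 0.21 SD. This treats the covariate as unstratified. Stratified allocation makes the part due to BMI category smaller.

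**Step 4: do the BMI-stratified analyses fill the gap?** If the strata are equal, each has about 11 women per arm, and the detectable difference is 2.80 × √(2/11) = 1.19 SD, against 0.845 SD overall. These analyses remove the BMI category difference inside each stratum, but their stated purpose is to see whether results differ by category. No combined, stratum-adjusted estimate is described, and baseline waist and percentage fat are still not used.

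**Step 5: the general sentence.** If a non-weight outcome were adjusted for baseline weight alone (correlation 0.2, assumed) instead of its own baseline (correlation r), the variance ratio would be (1 − 0.2²)/(1 − r²): 0.96/0.75 = 1.28 at r = 0.5 and 0.96/0.51 = 1.88 at r = 0.7. If the sentence instead means change from baseline, the ratio against own-baseline ANCOVA is 2/(1 + r): 1.33 at r = 0.5 and 1.18 at r = 0.7. The two readings lead to different analyses, and the text does not settle which is meant.

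**The case against.** The strongest reply has four parts.

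- **The t-test is valid.** Randomisation protects it. Stratified blocks limit imbalance in BMI category, and the stratified analyses take account of that category. This stands. A reader might infer that the visceral fat result will be biased, or that BMI category is ignored throughout. The article supports neither inference: only the pooled comparison leaves BMI category out, and the cost there is precision and residual within-stratum imbalance.
- **The gain is speculative.** This also stands. Correlations of 0.6 to 0.8 would give multipliers on the effective sample size of about 1.6 to 2.8 (1/0.64 and 1/0.36), but nothing in the documents supports that range. Those multipliers also compare with no adjustment at all, so they overstate what a baseline measure would add once BMI stratum is in the model.
- **Own baselines are not shown to be displaced.** A reader might infer from the general sentence that every other outcome is adjusted for baseline weight in place of its own baseline. The text does not establish this. Weight is the only outcome whose own model names that covariate, and there it is the right one. The diet and activity model names no covariate and is described as assessing change. What remains is an ambiguous phrase that is wrong for non-weight outcomes if taken literally.
- **Visceral fat is secondary.** It is absent from the abstract's outcome list, and waist is the marker that the article describes as valid for central adiposity. This limits the importance of the point. It does not justify leaving out covariates already collected.

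Nor can the point be set aside as detail left to an analysis plan that is not shown. The article names the test, and it is the named test that is inefficient.

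**Conclusion.** The point holds as an efficiency weakness in a stated secondary analysis. The overall visceral fat test omits the randomisation stratum and usable baseline adiposity measures, and no planned analysis supplies an adjusted overall estimate. Under assumed correlations of 0.5 to 0.7, adjustment would cut residual variance by 25% to 49%. BMI stratum alone would account for about 6% to 36% under the assumed stratum differences. These sizes are illustrative, because the documents contain no correlation or stratum difference for visceral fat. The missing baseline itself cannot be restored by analysis.

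The phrase about baseline weight is a secondary matter of wording. The analysis of weight, the primary outcome, is correctly adjusted for its own baseline and is not in question here.

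**What to change.** 1. Replace the visceral fat t-tests with ANCOVA at 12 and 24 months, or with a repeated-measures model over 12, 18 and 24 months that also uses the 18-month reading. Include BMI stratum and one prespecified baseline adiposity measure, such as waist circumference or percentage fat. These measures overlap, and with about 22 women per arm the covariates should be few. Name the chosen measure before group differences are examined.
2. Keep the BMI-stratified analyses, described as exploring whether results differ by category.
3. Reword the opening sentence of Data analysis so that each continuous outcome with a baseline measurement is adjusted for its own baseline value and BMI stratum, and name those covariates for the diet and physical activity models.

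The cost is a change of analysis wording. The covariates are already recorded, and no measurement, visit or sample size changes.
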